| Primary Objective                                  | To obtain preliminary data on the effects of acupuncture and sham acupuncture compared to usual care in reducing chemotherapy-induced peripheral neuropathy (CIPN) severity to help design a fully powered randomized trial.                                                                                                                                                                                                                                                                                                                                                                                                                                        |
| Secondary Objectives                               | 
To obtain estimates of the change in CIPN severity
 
To elucidate the mechanisms of acupuncture by obtaining estimates of tactile threshold, vibration threshold, thermal threshold and controlled pain modulation.
 
To obtain estimates of the change in insomnia, anxiety, depression, and fatigue symptoms.
 
To obtain estimates of the correlation of treatment expectancy and treatment response among patients who undergo acupuncture or sham acupuncture.
 
To estimate the proportion of patients with a dose reduction and the proportion with a dose escalation of neuropathy medication during the course of the 12 weeks.
 |
| Patient Population                                 | Solid tumor cancer survivors on no or stable neuropathy medication with persistent moderate to severe CIPN, defined as numbness, tingling, or pain ratings of $\geq 4$ on the numeric rating scale (NRS), at least 3 months after neurotoxic chemotherapy completion.                                                                                                                                                                                                                                                                                                                                                                                               |

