### **4.2 Intervention**

Subjects will be stratified based on the type of the most bothersome CIPN symptom (tingling vs numbness vs pain) and severity of such symptom (moderate 4-6 vs 7-10 on NRS) first. They will then be randomized at a 1:1:1 ratio to the acupuncture group (ACU), sham acupuncture group (SHAM) or usual care group (UC). Integrative Medicine Service acupuncturists will perform the acupuncture

and sham acupuncture treatments. The acupuncture group and sham acupuncture group will undergo 8 weeks of outpatient acupuncture or sham acupuncture treatments (twice weekly for 2 weeks, then weekly for 6 weeks, 10 treatments in total). We have designed this approach to standardize acupuncture treatment for future broad use; it is based on the understanding that CIPN is a global symptom complex rather than individual isolated or local symptoms. We will encourage all patients to keep their pain medication regimen unchanged during the 8-week intervention and will record all pain medication usage during the study. A window of  $\pm 3$  days applies to acupuncture sessions. A missed session will not be made up without prior approval from the PI. Highly experienced and licensed acupuncturists who are part of MSK's Integrative Medicine Service will perform the acupuncture or sham acupuncture treatments.

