## **6.0 CRITERIA FOR SUBJECT ELIGIBILITY**

### **6.1 Subject Inclusion Criteria**

- English-speaking
- Age  $\geq$  18 years old
- Solid tumor survivors with no evidence of disease
- Moderate to severe CIPN, defined by symptoms such as numbness, tingling, or pain ratings of 4 or greater on a 0-10 numeric rating scale (NRS)
- Have completed neurotoxic chemotherapy at least 3 months prior to enrollment
- If taking anti-neuropathy medications, they are on a stable regimen (no change in 3 months)

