### **Pain Medication List**

The pain medication list will be collected at baseline, and weeks 4, 8, and 12. The information can be captured via a phone call for the usual care group at week 4. The form lists the name and dosage of the neuropathy medication the patient is taking, if any. The lists will be compared before and at week 8 to determine if the medication was dose reduced or escalated. If the dosage or frequency resulted in total daily dosage increases, then it will be considered dose escalation. If the total daily dosage decreases, then it will be considered dose reduction. (Appendix D)

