## **10.0 EVALUATION DURING TREATMENT/INTERVENTION**

The study schema and study calendar are presented in Section 1.0., Figure 1 and Table 2, respectively. Validated patient-reported outcome questionnaires: Functional Assessment of Cancer Therapy/ Gynecologic Oncology Group-Neurotoxicity (FACT/GOG-Ntx) questionnaire, Neuropathy Pain Scale (NPS), and Numeric Rating Scale (NRS) for pain, tingling and numbness will be assessed at baseline, and weeks 4, 8, and 12 for the acupuncture and sham acupuncture groups. The Treatment Expectancy Scale (TES) will be completed at baseline, weeks 4, 8, and 12. The usual care control group will complete the questionnaires at baseline, and weeks 4, 8 and 12. CIPN severity will be assessed at baseline and weeks 8 and 12. The pain medication list will be collected at baseline, and weeks 4, 8, and 12. Both the quantitative sensory testing and Controlled Pain Modulation (CPM) will occur at baseline (+ 1 week), at the end of the 8-week treatment phase (+/-3 days), and at 12 weeks (+/-3days). All groups will complete the Insomnia Severity Index (ISI), Hospital Anxiety and Depression Scale (HADS), and Brief Fatigue Inventory (BFI) at baseline, and weeks 8 and 12. At the end of the study, patients in the true and sham acupuncture groups will complete the Study Allocation Belief Form, to guess which group they were assigned for evaluation of blinding to random assignment and why they believe that to be the case.

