neuropathy we will use linear regression to assess the association between NRS and TT, VT, and THT at baseline, and the association between change in NRS with change in TT, VT, and THT. For the mechanistic studies, we will use an interaction term between baseline CPM and real acupuncture to predict NRS at 8 weeks:  $NRS_8 = \beta_1 NRS_0 + \beta_2 CPM_0 + \beta_3 \text{Real Acupuncture} + \beta_4 CPM_0 \times \text{Real Acupuncture} + c$ . We will also test acupuncture-induced changes in CPM as  $CPM_8 = \beta_1 CPM_0 + \beta_2 \text{Real Acupuncture} + \beta_3 \text{Any Acupuncture} + c$ . We will also explore the relationship between treatment expectancy and response adjusting for baseline CIPN and treatment arm using multivariable linear regression comparing acupuncture versus sham acupuncture:  $NRS_8 = \beta_1 NRS_0 + \beta_2 \text{Real Acupuncture} + \beta_3 \text{Treatment Expectancy} + c$ . We will also estimate the change in mean HADS, BFI and ISI scores from baseline to 8 and 12 weeks along with a 95% confidence intervals, separately. We will also estimate the proportion of patients with a dose reduction and the proportion of patients who experience a dose escalation of neuropathy medication during the course of the 12 weeks along with an upper 90% confidence interval. All analyses will be by intent to treat, with participants analyzed according to allocation irrespective of treatment actually received. We will use multiple imputation, including 4 week outcome, for missing data at 8 weeks. Patients with 4 and 8 week outcomes are missing, they will not be included in the analysis.

For a trial with 25 patients per group, and an anticipated correlation between baseline and follow-up measures of 0.5, we will be able to calculate the upper bound of a one-sided, 90% confidence interval for the coefficients of any treatment and real acupuncture to approximately 0.35 standard deviations.

Last year, 935 solid tumor survivors had a diagnosis of persistent CIPN 3 months after chemotherapy completion. A recent study showed that among breast cancer survivors 28% reported moderate to severe CIPN 3 months after chemotherapy completion. Therefore, we anticipate 262 patients are eligible per year for our proposed study. Assuming at least a 15% enrollment rate of the eligible patients the estimated accrual is 3-4 patients per month, the estimated accrual period is between 19 and 25 months in order to identify 75 eligible patients.

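### The only rule for classifying a neuropathy-medication dose change stops at week 8, while the objective and the analysis report the proportions over 12 weeks

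*Protocol*

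**What the plan says.** The secondary objective, in Table 1 (Section 1.0) and again in Section 2.0, is to estimate the proportion with a dose reduction and "the proportion with a dose escalation of neuropathy medication during the course of the 12 weeks". Section 14.0 keeps that window for both directions of change; for escalation it plans an estimate for "patients who experience a dose escalation of neuropathy medication during the course of the 12 weeks along with an upper 90% confidence interval".

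The classification rule is under Pain Medication List in Section 8.0: "The lists will be compared before and at week 8 to determine if the medication was dose reduced or escalated". Two sentences then give the direction of change: "If the dosage or frequency resulted in total daily dosage increases, then it will be considered dose escalation", and "If the total daily dosage decreases, then it will be considered dose reduction". Neither of these names a time point.

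Collection runs to the end of the study. Section 10.0 states: "The pain medication list will be collected at baseline, and weeks 4, 8, and 12". The study calendar (Table 2) and Section 8.0 agree. Under Section 4.2 the trial encourages all patients to hold their pain medication steady "during the 8-week intervention and will record all pain medication usage during the study".

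**The concern.** The protocol fixes a classification rule and a reporting window, and the two disagree. This is not a detail left for a statistical analysis plan to supply, because both are stated here. An analyst following Section 8.0 and one following Section 14.0 could count different patients for the same objective.

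The omitted weeks are also not a random third of the study. Patients enter on no neuropathy medication or on a regimen stable for three months, and are then encouraged not to change it for the eight weeks of the intervention. Weeks 8-12 are the only study weeks free of that encouragement. A rule that stops at week 8 therefore looks only at the period in which change is discouraged, while the result carries a 12-week label.

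**Working it through.** There is no planned figure to reproduce, because the protocol gives no expected rate of dose change. The check is a comparison of texts, followed by the arithmetic for one patient.

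**Windows side by side**

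| Item | Place | Window |
|---|---|---|
| Objective | Table 1; Section 2.0 | 12 weeks |
| Analysis | Section 14.0 | 12 weeks |
| Classification rule | Section 8.0, Pain Medication List | to week 8 |
| Lists collected | Table 2; Sections 8.0 and 10.0 | baseline, weeks 4, 8 and 12 |
| Encouragement to keep medication unchanged | Section 4.2 | the 8-week intervention |

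Table 1 sets eight weeks of treatment and four weeks of follow-up, so the 12-week window cannot be another name for the treatment period. The rule leaves 12 - 8 = 4 of the 12 weeks uncovered. No other mention of dose change or of the medication list supplies a rule for week 12.

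**Direction of the effect**

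Take one direction of change, for example escalation. Let A be the patients who show it on a list up to week 8, and B those who show it on any list up to week 12. Every patient in A is also in B, so with a common denominator the proportion in A cannot exceed the proportion in B. The difference is made up of the patients who first show that change between weeks 8 and 12.

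This ordering depends on the quantity being any change during the 12 weeks. For net change from baseline to week 12 it fails: a patient who has changed at week 8 and is back at the baseline dose by week 12 is counted by the 8-week rule but has no net change.

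**Size per patient**

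Inputs: 75 patients in total and 25 per arm (Table 1). If k patients are missed, the shortfall is k/75 pooled, or k/25 within one arm.

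- One patient, pooled: 1/75 = 1.3 percentage points.
- One patient, within an arm: 1/25 = 4.0 percentage points.

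The number missed is not in the documents. For illustration only, assumed values of k = 0, 1, 3 and 6 out of 75 give shortfalls of 0, 1.3, 4.0 and 8.0 points pooled. The protocol does not say whether these proportions are pooled or reported by arm, so both denominators are assumptions.

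**The case against.** The best defence is that the mismatch is looser than it looks. The two sentences defining escalation and reduction carry no time window, and the week 12 list is collected, so an analyst guided by Section 14.0 could apply the definitions to that list and obtain a genuine 12-week proportion. Nothing would be lost, because the data will exist. This stands as a limit on the consequence: the 8-week result follows only if the Section 8.0 comparison is applied as written. It does not remove the contradiction, since that comparison is the only one the protocol states.

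A reader might also infer more than the text supports:

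- *That the rule ignores the week 4 list and so misses a change reversed by week 8.* This holds if the comparison is baseline against week 8. The wording can also be read as the lists before week 8 together with the one at week 8, which would bring week 4 in. Only the omission of week 12 holds on both readings.
- *That the reported figure is always too low.* This is true for any change, which is the natural reading of the objective, but not for net change to week 12.
- *That the planned upper 90% bound would fail to cover the 12-week proportion.* This needs a number of late changes, a grouping and an interval method, and the protocol gives none of them.
- *That fewer than 75 patients can contribute to the reduction proportion.* Patients on no neuropathy medication are eligible, but whether any enrol is not known from the protocol.
- *That encouraging stable medication is itself a fault.* It is sound design, and it matters here only because it makes weeks 8-12 different from the weeks before.

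**Conclusion.** The inconsistency is real and minor. Sections 8.0 and 14.0 cannot both be followed for a patient whose first change falls in weeks 8-12. Following Section 8.0 gives an 8-week proportion under a 12-week label. For any change during 12 weeks the error can only be an understatement, of 1.3 points per missed patient pooled or 4.0 points by arm, taking all 75 or all 25 patients as the denominator. The total cannot be derived from the documents.

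The effect is confined to one descriptive secondary objective of a pilot trial. The primary endpoint, the sample size and safety are unaffected.

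**What to change.** Amend the rule under Pain Medication List in Section 8.0 so that it matches the objective: escalation is any increase, and reduction any decrease, from baseline in total daily dosage on the week 4, week 8 or week 12 list. A comparison of baseline with week 8 may be kept if it is labelled as an 8-week result. The encouragement in Section 4.2 should stay.

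The cost is the rewording of one rule; no new data, visits or forms are needed. The remaining weakness is that a change made and reversed between two lists will still be missed.

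Relabelling the objective and the analysis as 8 weeks would also remove the contradiction, but it would give up the only weeks in which patients are not being encouraged to keep their medication unchanged.

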### **Quantitative Sensory Testing (QST)**

At weeks 0 (Baseline), 8 and 12, all participants will receive QST from a trained research study assistant (RSA). To minimize inter-observer variability in measurement, the same RSA will conduct all pre- and post-measurements for participants when possible. This RSA will be blinded to treatment allocation. Participants will be asked not to take any pain, stimulant, or sedative medication for at least 12 hours prior to the testing session. We will conduct QST in a quiet room with little environmental stimuli to detect tactile threshold (TT), vibration threshold (VT), and thermal threshold (THT). The TT and pressure pain threshold will be evaluated by means of Von Frey’s filaments (Somedic; Stockholm, Sweden), a set of 17 filaments with hairs of different diameters. We will ask the subject to sit in a comfortable position and close their eyes so that the examination is not influenced by visual input. TT will be assessed at the dorsum of the distal interphalangeal joint of the right- and left- middle fingers and both the left and right big toes, as described previously. The VTs will be assessed using a handheld biothesiometer (Bio-Medical Instrument Company; Newbury, Ohio), whose amplitude may be gradually increased until the threshold of vibratory sensation is reached. The VTs will be evaluated at the dorsum of the distal interphalangeal joints of the right

and left index fingers and both the left and right big toes. We will ask subjects to indicate when they feel the vibration stimulus for the first time (perception threshold) and when this stimulus disappears again (disappearance threshold). The average of three-paired measurements is considered to be the VT at the location investigated. The thermal threshold will be measured by the TSA-II system, which is a thermal sensory analyzer, providing for evaluation of cool sensation, warm sensation, heat-pain, and cold-pain thresholds. Its temperature (stimulation) range is 0 to 50°C, with a programmable stimulation rate of up to 8°C per second. Thermal thresholds will be assessed by the method of limits. First, the thermode will be attached and the skin will be allowed to adapt to a temperature of 32°C. For the sensory threshold assessment, the thermode will be warmed or cooled at a slow rate (1°C/s) until the subject perceives the first warm or cold pain sensation. For the heat-pain and cold-pain thresholds, we will increase/decrease the temperature at a rate of 2°C/s until the moment that the subject indicates the transition of the warm/cold sensation into a painful sensation. We will repeat each test three times and average the results to obtain the threshold value.

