| Study Allocation Belief                                                                                          |   |   |   | X |
| Pain Medication List                                                                                          | X | X | X | X |
| Safety Assessment                                                                                                | X | X | X |   |
| Quantitative Sensory Testing (QST)                                                                               | X |   | X | X |
| Controlled Pain Modulation (CPM)                                                                                 | X |   | X | X |

1. In the case of any missed sessions during the study, the testing, questionnaires and other assessments should occur in the same week as planned. In the case of early discontinuation of treatment, all attempts will be made to collect the questionnaires until the end of the study.
2. ECOG Performance Status will be assessed  $\leq 28$  days before the consent.
3. The medication lists will include both prescription and non-prescription pain medication.
4. Patients will be monitored for side effects at each acupuncture and sham acupuncture session .
5. This will be performed by an IMS research study assistant who will go through training before the initiation of the study. A window of + 1 week applies to the baseline assessments, and a window of +/- 3 days applies to week 8 and week 12 assessments.
6. Can be performed over the phone.

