## **4.0 OVERVIEW OF STUDY DESIGN/INTERVENTION**

### **4.1 Design**

This is a single-center, three-arm, phase IIB, pilot randomized controlled trial comparing acupuncture, sham acupuncture and usual care. We will enroll 75 solid tumor cancer survivors who completed chemotherapy at least 3 months prior who have persistent moderate to severe CIPN symptoms defined as at least one NRS  $\geq 4$  (25 patients in each arm). With a total sample size of 75 this trial will provide preliminary data on the effects of treating patients with acupuncture to reduce persistent CIPN as measured by NRS and other CIPN measurements such as NPS and FACT/GOG-Ntx when compared to sham acupuncture or usual care. The primary end point of this study is NRS of the patients' most bothersome CIPN symptom (tingling, or numbness or pain) at week 8. It is the CIPN symptom having the maximum NRS measured at baseline. If more than one symptom share the maximum value, we would ask the patient to pinpoint the most bothersome symptom and use that one as the primary endpoint. Secondary end points are NPS, FACT/GOG-Ntx, ISI, HADS, BFI, TES, QST and CPM. These data will then be used in the design of a fully powered trial.

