## **15.2 Randomization**

Randomization is implemented via MSKCC's Clinical Research Database (CRDB), a secure system that ensures that treatment allocation cannot be guessed before or modified after a patient is registered on trial, allowing for full allocation concealment. Randomization will be 1:1:1 (ACU:Sham: UC) using randomly permuted blocks of random length stratified by type of the most bothersome CIPN symptom (tingling vs numbness vs pain) and severity of such symptom (moderate 4-6 vs 7-10 on NRS). Once the patient is randomized, the CRS or CRM will inform the acupuncturist of the patient's group assignment and the RSA of whether the patient was assigned to an acupuncture group or to the UC group. The RSA's and patients will be blinded to which acupuncture group the patient was assigned. The acupuncturists will be the only ones unblinded. The rest of the study co-investigators and staff will remain blinded.

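### The QST tester is described as blinded, but section 15.2 tells the RSA who is in usual care, so on the natural reading assessor blinding covers only real versus sham acupuncture

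*Protocol*

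**What the plan says.** Three places in the protocol bear on what the tester knows.

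- **Section 8.0, QST.** A trained RSA tests every participant at baseline and at weeks 8 and 12, if possible the same RSA each time. The masking claim carries no exception for usual care: "This RSA will be blinded to treatment allocation".
- **Section 1.0, Table 2, footnote 5.** The footnote is attached to both the QST row and the CPM row: "This will be performed by an IMS research study assistant who will go through training before the initiation of the study".
- **Section 15.2.** Once a patient is randomised, the CRS or CRM tells the acupuncturist the assigned arm and also informs "the RSA of whether the patient was assigned to an acupuncture group or to the UC group". The masking that remains is then described: "The RSA's and patients will be blinded to which acupuncture group the patient was assigned". The next sentence reads: "The acupuncturists will be the only ones unblinded".

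The design in section 4.1 is a three-arm "pilot randomized controlled trial comparing acupuncture, sham acupuncture and usual care", with 25 patients per arm. QST and CPM are listed there as secondary endpoints. Section 3.0 presents QST as an objective marker and gives the study of acupuncture's effect on it as one purpose of including it.

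**The concern.** A tester who has been told which patients are in usual care is not blind to allocation in a three-arm trial. The tester is blind to one distinction, real versus sham, and not to the other. Section 8.0 claims the full property; the procedure in section 15.2 delivers only the partial one. Section 15.2 also conflicts with itself, because it gives UC status to the RSA and then says that only the acupuncturists are unblinded.

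What is at stake is how the mechanistic results are read. UC patients cannot be masked, so keeping the tester unaware of UC status is the main protection left for comparisons with that arm. Some of the tests leave room for the examiner's technique, notably the hand-applied filaments and the handheld vibration device. If the report repeats section 8.0, a difference from UC on QST would be described as assessor-blinded when the protocol's own notification step says otherwise.

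This is not a detail to leave to a statistical analysis plan. Who is told the allocation is a trial procedure, and the protocol settles it in two incompatible ways.

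**Working it through.** No sample size, power or error-rate figure is involved, so the check sets the texts side by side and then counts the comparisons affected.

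**Step 1. Who tests, and what that role is told.**

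| Question | Place | Answer |
|---|---|---|
| Who performs QST? | Section 8.0; Table 2, footnote 5 | An RSA |
| Who performs CPM? | Table 2, footnote 5 | An RSA |
| What masking is claimed for the QST tester? | Section 8.0 | Full, no exception |
| What masking is claimed for the CPM tester? | Section 8.0, CPM text | None stated |
| What is the RSA told? | Section 15.2 | UC, or one of the two acupuncture arms |
| What stays hidden from RSAs? | Section 15.2 | Real versus sham |
| Is a separate masked tester named? | Nowhere in the protocol | No |

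**Step 2. What the RSA knows, patient by patient.** Allocation is 1:1:1 with 25 per arm, 75 in total. For the 25 UC patients the RSA knows the exact arm. For the other 75 − 25 = 50, the RSA knows only that the arm is real or sham acupuncture.

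**Step 3. Pairwise comparisons.** Three arms give 3 × 2 / 2 = 3 pairs.

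- Acupuncture versus sham: tester masked.
- Acupuncture versus UC: tester not masked.
- Sham versus UC: tester not masked.

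**Step 4. The CPM model in section 14.0.** Week-8 CPM is regressed on baseline CPM, Real Acupuncture (coefficient β2) and Any Acupuncture (coefficient β3). Taking the indicators in the order of the equation, acupuncture is 1/1, sham 0/1 and UC 0/0. At equal baseline CPM:

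- Acupuncture − sham = (β2 + β3) − β3 = β2. This rests on masked testing.
- Sham − UC = β3 − 0 = β3. This rests on testing by someone told who is in UC.
- Acupuncture − UC = β2 + β3. This inherits the problem through β3.

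Of the two coefficients that the CPM model estimates, one is affected.

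**Step 5. QST.** Section 14.0 writes out no between-arm model for QST, only its association with NRS. A QST comparison between arms follows from the purpose stated in section 3.0 and the endpoint list in section 4.1. The count in step 3 shows which comparisons would lack assessor masking if made; it is not a list of planned analyses.

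**The case against.** The strongest reply is that no sentence says the RSA who is informed is the RSA who tests. Section 7.0 refers to RSAs in the plural, section 16.0 names a primary RSA with broad data duties, and section 8.0 could mean a different, trained RSA. This stands as a limit: a reader might infer that the tester is unblinded as a matter of fact, and the documents do not go that far. They do use one role name throughout, describe the masking of RSAs as a group, and define no separate tester. Even on the kinder reading, the separation on which section 8.0 depends is not written down.

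Further points are fair:

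- Section 15.2 states the true level of masking openly, and its remark about the acupuncturists can be read as referring to real versus sham only. That softens the internal conflict but does not reconcile section 8.0.
- The blinding sentence stands under QST. The CPM text claims no masking, so it would be wrong to say that the protocol calls CPM testing blinded. CPM comes in only because footnote 5 gives it to the same role.
- Thermal stimuli run at programmed rates and end on the patient's response, and CPM scores are the patient's own ratings. Examiner influence is less plausible there than for filaments and vibration.
- Section 9.0 lets an acupuncturist or an RSA collect adverse effects around sessions. This is a possible second route to knowing who is being treated, but it does not name the tester.

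A reader might also infer that the trial's main result is compromised. The documents do not support that. The primary endpoint is the patient's own NRS rating at week 8, and the definitive trial foreseen in section 14.0 is acupuncture versus sham, where masking holds.

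**Conclusion.** The point holds in a limited form. Sections 8.0 and 15.2 contradict each other on what the QST tester knows. On the natural reading, testing is assessor-blinded for acupuncture versus sham and is not for either comparison with usual care. That applies to the secondary QST measures and to CPM, where the sham-versus-UC coefficient is the one affected.

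This rests on one assumption: that the RSA informed under section 15.2 may also be the tester. Nothing in the protocol rules that out. The documents give no basis for a numerical size of any resulting bias, and none is claimed. UC patients know their own arm, so these response-based tests remain open to that influence against UC whatever the tester knows. Masking the tester would remove one source of bias, not all of it.

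**What to change.** **Preferred.** In section 15.2, send the information that separates UC from the acupuncture arms only to staff who do not perform QST or CPM. State there and in section 8.0 that the tester does not receive it and does not collect adverse effects at treatment sessions. Amend the sentence on who is unblinded so that it matches. The cost is re-routing one message and separating duties among existing staff. The protocol does not give the number of RSAs, so whether this is feasible is for the sponsor to confirm.

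**If staffing does not allow it.** Correct sections 8.0 and 15.2 to say that RSAs are blinded to real versus sham acupuncture only, and report QST and CPM comparisons with usual care as not assessor-blinded. This is a wording change and needs no extra staff.

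Neither option touches the randomisation, the sample size or the primary analysis.

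### The stopping point of the 1°C/s thermal sensory run names pain on the cold side, which contradicts its purpose and, followed literally, leaves cool sensation unmeasured

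*Protocol*

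**What the plan says.** Under Quantitative Sensory Testing in section 8.0, the protocol describes the thermal device as "providing for evaluation of cool sensation, warm sensation, heat-pain, and cold-pain thresholds". That makes four separate quantities. "Thermal thresholds will be assessed by the method of limits", starting after "the skin will be allowed to adapt to a temperature of 32°C".

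Two kinds of run follow. The first is presented as the one for sensory thresholds, and its instruction is that "the thermode will be warmed or cooled at a slow rate (1°C/s) until the subject perceives the first warm or cold pain sensation". The second is described in these words: "For the heat-pain and cold-pain thresholds, we will increase/decrease the temperature at a rate of 2°C/s", and it continues "until the moment that the subject indicates the transition of the warm/cold sensation into a painful sensation". The closing rule is "We will repeat each test three times and average the results to obtain the threshold value".

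Testing takes place at baseline, week 8 and week 12. Thermal threshold is named in the mechanistic secondary objective in section 2.0. In section 14.0 it enters the exploratory regressions on NRS, including "the association between change in NRS with change in TT, VT, and THT".

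**The concern.** Under the method of limits, the recorded threshold is the temperature at which the run is stopped. The stopping instruction is therefore the definition of the variable. Here the run meant to find when a patient first feels a temperature change is told, at least on the cold side, to continue until pain.

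Detection and pain thresholds answer different questions. Section 3.0 justifies sensory testing as a measure of small-fibre impairment, and numbness is one of the three symptoms that define eligibility and stratification. The same section also lists hyperalgesia and allodynia as features of the condition, and these concern pain responses. If a cold-pain temperature is stored under a detection label, the planned association between NRS and thermal threshold would be read as something it is not.

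An analysis plan cannot repair this later, because a first-cool temperature that was not captured at the visit cannot be recovered. The protocol also promises the same assistant for a patient's repeated tests only when possible. Two assistants who understood the sentence differently could apply different endpoints to one patient before and after treatment, and the change score would then mix two variables.

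**Working it through.** There is no stated figure to reproduce. The check sets the four listed thresholds against what each run would yield under each way of reading the 1°C/s instruction.

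Inputs, all from Quantitative Sensory Testing in section 8.0: four listed thresholds; a 32°C start; a 1°C/s run with the endpoint in question; a 2°C/s run ending when warm or cold turns painful; three repeats averaged.

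- **Reading A:** warming stops at first warmth, cooling stops at cold pain.
- **Reading B:** the word for pain governs both directions, so both stop at pain.
- **Reading C:** the word for pain is a slip, and both directions stop at first sensation.

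| Listed threshold | Reading A | Reading B | Reading C |
|---|---|---|---|
| Cool sensation | not recorded | not recorded | 1°C/s run |
| Warm sensation | 1°C/s run | not recorded | 1°C/s run |
| Heat pain | 2°C/s run | 1°C/s and 2°C/s runs | 2°C/s run |
| Cold pain | 1°C/s and 2°C/s runs | 1°C/s and 2°C/s runs | 2°C/s run |
| Listed thresholds obtained | 3 of 4 | 2 of 4 | 4 of 4 |

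Readings A and B are the two that keep the sentence as printed. Under both, the cold side of the sensory run ends at pain and no run gives cool sensation. Only Reading C delivers the listed set, and it requires deleting a word.

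Nothing elsewhere supplies the missing endpoint. The study calendar, section 10.0 and section 14.0 refer to the testing without defining it. The pain modulation test in section 8.0 uses the same device, but for a heat-pain stimulus.

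Reach if the text is followed literally: 75 planned patients × 3 visits = 225 planned assessments, each lacking cool sensation.

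The protocol gives no temperatures from which to size the error in a recorded value. For illustration only, assume cool detection at 27 to 31°C and cold pain at 5 to 20°C. The gap then runs from 27 − 20 = 7°C to 31 − 5 = 26°C. Neither range comes from the document, and the conclusion does not depend on them.

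**The case against.** The strongest reply is that this is a stray word in a paragraph whose intent is clear. The protocol lists cool sensation separately from cold pain, labels the slow run as sensory, and gives the pain thresholds their own run and ramp. The pain-run endpoint treats warm or cold sensation as something that comes before pain. The study calendar notes say that the assistant is trained before the study starts. Such a person may well stop the slow run at first coolness whatever the sentence says.

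Most of this stands. It makes Reading C the likeliest intention, so it would be wrong to state that cool sensation will be lost in every patient; that holds only if the sentence is followed as printed. The reply does not remove the conflict, because the sentence is an operating instruction and nothing in the document corrects it.

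A reader might also infer that section 14.0 merges the four thresholds into a single thermal variable, in which warm and cold shifts would partly cancel. The protocol does not support that. The abbreviation THT is introduced simply as thermal threshold, alongside the tactile and vibration thresholds, each of which also covers several sites. No averaging or summing across thermal modalities is stated, and no equation is given for this regression. How the components enter the model is ordinary analysis-plan detail, so section 14.0 needs no change on this account.

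**Conclusion.** The point holds as an internal contradiction in an operative measurement rule. As printed, the 1°C/s endpoint is inconsistent with the label of the run, with the listed cool-sensation threshold and with the separate 2°C/s cold-pain run. Followed literally it costs one of four thermal thresholds, or two if pain governs both directions. The two cold-pain values would not be simple replicates either, since they are taken at different ramp rates.

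Confidence is high for the textual conflict. Actual data loss is conditional on the assistant following the printed sentence, which the document neither confirms nor rules out.

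The consequence is limited. Only the thermal part of sensory testing is affected, and it serves a secondary mechanistic objective and exploratory regressions in a pilot trial. The tactile and vibration thresholds, the pain modulation outcome, the 2°C/s pain thresholds, the primary NRS endpoint and the sample size are unaffected.

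**What to change.** In Quantitative Sensory Testing, section 8.0, state that the 1°C/s run ends at the first warm or cool, non-painful sensation. Keep pain as the endpoint only for the 2°C/s runs. Make the same change in the assistant's test script, so that all assistants record the same response at all three visits.

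The cost is one corrected phrase in each place. No test, visit, patient or testing time is added, because both kinds of run are already planned with three repeats each. The correction needs to be in place before testing, since a missed detection temperature cannot be recovered afterwards.
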